### Withdrawal of individual subjects and replacement

A study subject can stop the study at any time without explanation, this will have no consequences. The investigator can decide to withdraw a subject from the study for urgent medical reasons, non-compliance with the study procedures or pregnancy. There will be no replacement for withdrawn individuals. In principal a LLETZ will be performed, since this is still the standard treatment for patients with recurrent or persistent CIN lesions.

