### Interventions

Patients will receive verbal and written information about the study procedure. They have to sign an informed consent, where after patients are randomized into the intervention arm or the standard treatment:Intervention arm: Imiquimod treatment. Patients in this group have to insert imiquimod 5% cream intravaginally for 16 weeks.Standard treatment. A LLETZ procedure is performed according to the current guidelines.

Patients in the imiquimod treatment group will apply imiquimod 5% cream intravaginally during 16 weeks. One sachet contains 12,5 mg of imiquimod and is applied with a vaginal applicator. The application frequency is 3 times a week. Patients get instructions and administer the cream themselves, before bedtime. The patients are advised to take an intravaginal shower with an applicator the next morning in order to remove cream leftovers, followed by an external shower to remove any remains on the vulva. Anti-inflammatory drugs (paracetamol or NSAID) can be used in case of mild systemic drug-related side effects. If the local or systemic side effects persist or are severe, patients are advised to reduce the frequency of the imiquimod insertion, first twice weekly, subsequently once weekly. Imiquimod treatment is discontinued for maximum of a week in case of persistent side effects. In order to prevent pregnancy, patients are advised to use adequate contraception. Subjects should refrain from vaginal sexual intercourse during the nights that imiquimod is applied until the vaginal shower the next morning. After 10 weeks a colposcopy is performed to rule out disease progression. Biopsies are only performed in case of suspicion of invasive disease.

In the standard treatment group, patients will undergo a LLETZ procedure within 4 weeks after the diagnosis. Excision of macroscopic lesions and the transformation zone will be achieved by a monopolar loop electrode, preferably under local anaesthesia.

Treatment efficacy is evaluated at 26 weeks follow-up for both groups. The Imiquimod group will have a Pap smear and a colposcopy with diagnostic biopsies. Biopsies are performed at the initial CIN lesion site and at any other suspect site, with a minimum of two. In case of persistent or progressive disease, surgical excision is performed. The LLETZ group will have follow-up with cervical smears at 6, 12 and 24 months according to the current guidelines.

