### Blinding

The study is single blinded: the pathologists evaluating cytological and histological samples are blinded with respect to the intervention.

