### Statistical methods

Analysis will be done according to the intention to treat principle and the non-inferiority principle to show that imiquimod is not worse than an existing treatment (LLETZ). To investigate efficacy we will perform a per protocol analysis (although this is not the primary outcome of the study). The primary outcome is the difference between the probability of regression in the LLETZ and the imiquimod arms. The expected difference (LLETZ-imiquimod) will be calculated together with the 95% Aggresti confidence interval. If the upper bound of the interval lies below the non-inferiority margin of 10% non-inferiority of the imiquimod treatment is assumed to be proved. Logistic analysis of potential confounders (age at diagnosis, CIN grade, number of previous treatments, smoking, HPV-subtype) will be performed. Analysis will be based on intention to treat protocol.

The prevalence and severity of side effects of imiquimod and LLETZ treatment, as documented according to Common Terminology Criteria for Adverse Events guidelines, will be presented as proportions and means with 95% confidence intervals. Differences in the rates of overall side-effects and severe side-effects between the imiquimod and LLETZ groups will be tested with a chi-square test. Disease recurrence rates, defined by abnormal cervical cytology, after 6, 12 and 24 months will be evaluated in adequately treated patients by use of multiple logistic regression analysis, after adjustment for age at diagnosis, CIN grade, smoking sexual behavior and HPV subtype.

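### Unblinded investigators may withdraw patients from the study for non-compliance or pregnancy, with no provision for keeping their outcomes, which conflicts with the intention-to-treat primary analysis

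*Protocol article*

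**What the plan says.** Under *Withdrawal of individual subjects and replacement*, the protocol article says: "The investigator can decide to withdraw a subject from the study for urgent medical reasons, non-compliance with the study procedures or pregnancy". It continues: "There will be no replacement for withdrawn individuals". On treatment afterwards it says: "In principal a LLETZ will be performed, since this is still the standard treatment for patients with recurrent or persistent CIN lesions". The section has no category for a patient who is off study treatment but still followed, and it does not mention the withdrawn patient's week-26 smear.

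Under *Blinding*, the masking covers one group: "the pathologists evaluating cytological and histological samples are blinded with respect to the intervention". Nothing masks the investigator who decides on withdrawal.

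Under *Statistical methods*, the primary analysis is fixed: "Analysis will be done according to the intention to treat principle and the non-inferiority principle". The section repeats the intention-to-treat basis later. The other analysis is supportive: "To investigate efficacy we will perform a per protocol analysis (although this is not the primary outcome of the study").

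Under *Interventions*, imiquimod is self-inserted three times a week for 16 weeks, and LLETZ is one procedure within four weeks of diagnosis. The *Data collection* lists for weeks 10 and 26 record treatment compliance for the imiquimod group only.

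**The concern.** Non-compliance and pregnancy occur after randomisation, and non-compliance may be a consequence of the assigned treatment. An intention-to-treat analysis is meant to keep such patients in their assigned arm. A rule that lets an investigator who knows the arm take them out of the study works against it. This is a conflict between two stated rules, not a detail left out of a condensed article.

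The two arms are unequally exposed. A LLETZ patient can miss a visit, but after one procedure she has little treatment left to fail to comply with. An imiquimod patient has 16 weeks of dosing in which to fall short. That withdrawals will fall mainly on the imiquimod arm is therefore an inference, but the design supports it.

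If poor compliers regress less often and their outcomes are missing from the comparison, the remaining imiquimod patients look better than the randomised group. In a non-inferiority trial that favours accepting an inferior treatment. The planned per-protocol analysis would not expose this, because it selects on compliance too.

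**Working it through.** **The passages together.** The withdrawal rule takes the patient out of the study, is discretionary, and names non-compliance. The analysis rule requires all randomised patients. Nothing in the article links the two by saying that a withdrawn patient's outcome is still collected and analysed.

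**Inputs from the protocol article.** LLETZ regression 63%, margin 10 points and 174 per arm (*Sample size calculation*). Non-inferiority is declared if the upper 95% bound for LLETZ minus imiquimod is below 10 points (*Statistical methods*), which is a one-sided 2.5% test. The 174 serves here only as the planned analysed number. It does not follow from the stated 63%, 60%, 10 points and 80% power (758 per group at one-sided 2.5%, 597 at one-sided 5%), but that is a separate matter.

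**Assumed inputs, not in the article.** True imiquimod regression over all randomised patients is 53%, exactly at the margin (63 - 10), so a correct analysis errs 2.5% of the time. A fraction w of the imiquimod arm is withdrawn (10-20%) and would regress at rate q (20-40%). No LLETZ patient is withdrawn.

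**Formulas (normal approximation).**
- Withdrawn patients left out: p = (0.53 - wq)/(1 - w), with n = 174(1 - w).
- Withdrawn patients kept, given LLETZ, and scored on the later smear at an assumed 63%: p = 0.53 - wq + 0.63w, with n = 174.
- Withdrawn patients kept and counted as failures: p = 0.53 - wq, with n = 174.
- SE = √[0.63×0.37/174 + p(1 - p)/n].
- P(declare non-inferiority) = Φ[(0.10 - (0.63 - p))/SE - 1.96].

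**Middle case, left out (w = 15%, q = 25%).** p = (0.53 - 0.0375)/0.85 = 0.579, so the true 10-point deficit appears as 5.1 points. n = 147.9 and SE = 0.0547. Then 0.0494/0.0547 - 1.96 = -1.056, and Φ = 14.6%.

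| w, q | Left out: p, P | Kept, smear after LLETZ scored: p, P | Counted as failures: p, P |
|---|---|---|---|
| 10%, 40% | 54.4%, 4.5% | 55.3%, 6% | 49.0%, 0.3% |
| 15%, 25% | 57.9%, 14.6% | 58.7%, 19% | 49.3%, 0.4% |
| 20%, 20% | 61.3%, 32.1% | 61.6%, 38% | 49.0%, 0.3% |

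The correct value in every row is 2.5%. If withdrawn patients regressed at the same 53% as the rest, leaving them out would give p = 53% and no inflation. The bias needs both selective removal and a lower regression rate.

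The third column bears on the remedy. The article gives withdrawn patients LLETZ in principle. Keeping them in follow-up and scoring a smear taken after that LLETZ credits imiquimod with the control treatment's effect, and the error is then slightly larger than when they are left out.

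**The case against.** The strongest objection is that the article nowhere says week-26 data stop at withdrawal, or that withdrawn patients leave the analysis. It names intention to treat twice, records imiquimod doses, and plans a separate per-protocol analysis, so some poor compliers are evidently expected to stay in the data. Withdrawal is something the investigator may do, not must do. A statistical analysis plan that is not shown could count withdrawn patients as failures. All of this stands, and it makes the bias conditional. It does not remove the conflict: withdrawal from the study ordinarily ends follow-up, the article provides nothing to the contrary, and an analysis plan cannot recover smears that were never taken.

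A reader might also link the limit on treatment breaks ("Imiquimod treatment is discontinued for maximum of a week in case of persistent side effects") to removal, inferring that a patient who cannot restart becomes non-compliant and is taken off study. The article does not say so. It allows stepping down to twice and then once weekly for side effects, so reduced dosing is within protocol. Non-compliance is worded as concerning study procedures, which can include missed visits in either arm. The point does not need this link.

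Finally, the removal fractions and regression rates have no source in the article. Its only attrition figure is a 20% allowance for loss to follow-up across the whole trial. The table shows sensitivity and does not forecast what will happen.

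**Conclusion.** The point holds as a conflict between two stated rules. An unblinded investigator may withdraw patients from the study for non-compliance or pregnancy, and the primary analysis is by intention to treat. The rule can remove outcomes selectively from the imiquimod arm.

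The size is conditional. With true rates of 63% and 53%, 174 per arm, and 10-20% of the imiquimod arm left out at 20-40% regression, false non-inferiority rises from 2.5% to about 4.5-32%. If withdrawn patients are counted as failures, there is no inflation.

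A reader might infer that the rule certainly strips these outcomes and that the stated intention-to-treat analysis is therefore defeated. The article does not support that: it permits withdrawal and is silent on what happens to the data afterwards. The change is still worth making now, because recruitment has started and a missed primary outcome cannot be collected later.

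**What to change.** Reconcile *Withdrawal of individual subjects and replacement* with *Statistical methods*:

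- State that withdrawal for non-compliance, pregnancy or medical reasons does not end outcome collection and does not remove the patient from the intention-to-treat analysis. Only withdrawn consent ends data collection.
- Keep these patients in follow-up for the week-26, 12-month and 24-month cytology, and record the date of and reason for withdrawal.
- In the primary analysis, count an imiquimod-arm patient who received LLETZ before the week-26 assessment as not regressed, because a smear after LLETZ reflects the control treatment. Retention without this rule does not cure the bias.

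The clinical grounds for stopping imiquimod stay with the sponsor. The request concerns only outcome retention and scoring.

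The cost is protocol wording and one e-CRF field; cytology at these times is already scheduled. The imiquimod result may become less favourable.

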### Ethical considerations and dissemination

The standards outlined in the Declaration of Helsinki are guidelines for the study. Before the start of the study there was approval of the ethics committee. There is a data management safety board throughout the study. We will record adverse events and reported them to local protocol. We will be offering the study results for publication in international medical journals. If the subject agreed on this, study results will be communicated to trial participants by mail.

## Discussion

The development of a non-surgical treatment modality for residual and recurrent CIN lesions will lower the amount of LLETZ procedures for this indication and complications as a result of surgical intervention. Evidence shows that 15–22% of high-grade CIN lesions will persist or recur after 2 years and that patients after treatment for high grade CIN lesions will remain at higher risk for cervical cancer in the future. Based on earlier studies, we hypothesize that at least 50% of patients with high grade CIN will benefit from immunotherapy with imiquimod. The current study aims to test the treatment effectivity, while also assessing the clinical applicability of imiquimod treatment by documentation of side effects and quality of life associated with treatment.

## Abbreviations

CIN: Cervical Intraepithelial Neoplasia
HPV: Human Papillomavirus
LLETZ: Large Loop Excision of the Transformation Zone
VIN: Vulvar Intraepithelial Neoplasia
